#### Online scenario-based task: CBM-I and control condition materials

*CBM-I materials*: The two CBM-I conditions (CBM_RNT and CBM_STAND) consist of participants listening to scenarios describing situations relating to common worry-related (GAD group) and rumination-related (MDD group) themes which are initially emotionally ambiguous and which are resolved in either a positive manner (76% of the time), negative manner (12%) or which are left unresolved (12%) by the final word or short phrase of the scenario. Positive scenarios constitute the training scenarios and are designed to promote positive interpretations of ambiguous events; negative scenarios are included to ensure that participants attend carefully to the content of the scenarios. Previous research has shown that negative trials do not interfere with learning and may be helpful by providing an intermittent reinforcement contingency.^16^
^45^ Following each scenario, participants respond to a Yes/No question related to the content of the scenario. On positive and negative trials, participants receive feedback as to whether their response was correct or incorrect, that is, in line with the intended interpretation provided at the end of each scenario. This serves to reinforce the interpretation. The 12% unresolved scenarios serve as ‘test’ trials. On ‘test’ trials, participants do not receive feedback, but their response is recorded as an indicator of interpretation bias.

Worry scenarios were adapted from Mathews and Mackintosh,^16^ Hirsch, Hayes and Mathews,^18^ Hayes, Hirsch, Krebs and Mathews,^17^ and [name] (personal communication, 21 July 2015), while rumination scenarios were adapted from Holmes, Mathews, Dalgleish and Mackintosh,^46^ Hertel, Mor, Ferrari, Hunt and Agrawal,^19^ and Blackwell *et al.*^25^ In addition, further scenarios were created by the authors, resulting in 500 unique worry-related and 500 unique rumination-related scenarios. A subset of these scenarios was piloted online in N=92 participants in the general population using the crowdsourcing platform Amazon Mechanical Turk. Scenarios were presented without the disambiguating ending and participants suggested words to complete the scenarios. This approach was taken to ensure that scenarios were (1) well balanced, that is, had the potential to be disambiguated in a positive or negative manner (although during CBM-I, positive interpretations were selectively trained) and (2) were constructed to lead to relatively specific interpretations being made (rather than a wide range of possible interpretations). Scenarios were amended on the basis of these responses and a further subset was reviewed by expert researchers in rumination and worry as well as individuals with lived experience of GAD and depression.

All scenarios are around 50 words long. Worry-related scenarios cover three main themes of worry, namely performance, social relationships and physical threat, including illness and harm, as well as other common themes such as financial worries.^47^
^48^ Rumination-related scenarios cover three main rumination themes, namely feeling low (ie, ruminating about depressive symptoms^49^), abilities (relating to personal failure^5^) and social relationships (eg, ref. 50) as well as other themes linked to depressive symptoms such as feelings of guilt/shame. Example worry and rumination-related scenarios with corresponding questions are presented in table 1.

**Table 1 BMJOPEN2016013404TB1:** Example scenarios for worry-related and rumination-related CBM-I and active control conditions

	Scenario type	Scenario	Benign ending*	Negative ending†	Question	Benign/correct answer
Worry	Social relationships	You haven’t socialised much with the other members of your fitness class but following a good workout, you all go out for lunch. Later, when you are walking out of the restaurant, you overhear two members of the class talking about you. As you listen, you hear them saying that they think you are…	Alright	Boring	Do the other team members dislike you?	No
	Performance	You are learning how to use a new piece of software and have been completing tutorials online. The test is coming up in a few days and thinking about the amount of effort you have put in, you know you will do…	Very well	Badly	Will you fail the test?	No
	Illness and harm	You are walking down the road to your house late at night when you fall over and scrape your knee. When you look up, a group of teenagers are walking towards you. One of them reaches into their pocket and pulls out a…	Tissue	Knife	Did the teenagers help you?	Yes
	Test‡	Your flatmate is working late so you are in the house on your own this evening. You have just switched off the lights and got into bed when you hear a scraping in the lock of the front door. As you slowly approach the front door, it opens and you see what was causing the noise.	–	–	Is your flatmate home from work?	Yes
Rumination	Social relationships	At the bus stop, you bump into someone from your school days. They comment on how much you have changed since they last saw you. Mulling it over later, you think about their tone of voice and decide that they meant their comment to be…	Complimentary	Hurtful	Did the person intend to be mean?	No
	Abilities	You overhear someone at work saying that the company is making a few people redundant. You start thinking about the contribution you have made to the team since you started working at the company, and as you think it over, you suspect that you will be…	Safe	Made redundant	Will you be sacked?	No
	Feeling low	You are feeling quite exhausted. On social media, you see a photo of you when you felt better. As you think back to that time, you wonder whether in the future there will be times when you will feel less exhausted and you can see that there is…	Hope	Little prospect	Will you always be tired?	No
	Test	Your work contract is coming to an end. A colleague offers to organise leaving drinks for you and they email round the office to ask who is free. As you think back over your relationships with your colleagues, you can guess how many people are likely to come along.	–	–	Will a lot of people come along to your leaving do?	Yes
Control§	Ambiguous	You went on holiday with two friends. Your friends planned to go to a particular place, but you'd been there before and so a new destination was found. Looking back, you wonder whether your friends minded changing the plans for you.	–	–	Did your friends resent having to change the plans?	No
	Fact	Your mother lends you her brand new suitcase to take on a plane journey. You try to look after it but when you arrive at your destination, you see the case is damaged. As you contemplate telling your mother, you know who she will blame for the damage.	–	–	Did you take the suitcase on the train?	No

*In 76% of trials, the scenarios are provided with a benign ending.

†In 12% of trials, the scenarios are provided with a negative ending.

‡Test trials remain ambiguous and make up the final 12% of trials. Participants’ response to the test trial question indicates the interpretation they have made.

§While all CONTROL scenarios remain ambiguous, 50% are followed by questions that assess participants’ interpretation of the scenario (including disorder-specific test trials as above) and 50% relate to other fact-based information in the scenario that is not ambiguous and is emotionally neutral.

Within each online session, scenarios are presented in a pseudorandom order. The first half of each session (first 25 scenarios) includes scenarios from all themes. The second half of each session (remaining 25 scenarios) is matched to participants' concerns on the day. Participants select one of the main themes outlined above at the start of the session; this is also the theme participants will worry/ruminate about if they are in the CBM_RNT condition. The second half of the session then primarily presents scenarios relating to the selected theme. The number of different trial types (positive/negative/‘test’ trials) is kept constant in both halves of the session.

*Active control materials**:* To control for listening to scenarios and answering questions relating to the scenarios, the control condition consists of participants hearing ambiguous scenarios in which the ambiguity is not resolved, and which thus should not change interpretation bias. To match the control condition as closely as possible to the CBM-I conditions, each session contains scenarios adapted from worry and rumination materials, with the endings amended so that the ambiguity is left unresolved. As in the CBM-I conditions, participants hear 50 scenarios per session. Each scenario is either followed by a Yes/No question relating to the ambiguity of the scenario, which is not followed by feedback (similar to the ‘test’ trials), or relating to a factual element of the scenario, which is followed by feedback regarding whether participants' responses were incorrect. Both questions are designed to encourage participants to process the meaning of the scenarios. In addition, the ‘test’ trials from the CBM-I conditions will be included so that interpretations made across the course of the sessions can be compared between CBM-I and control conditions. Thus, we can also examine whether participants in the control condition impose their (default) negative interpretive style on the scenarios and whether there are any inadvertent training effects, such as participants in the control condition generating more positive or negative interpretations across the sessions. Example control scenarios with the different question types are presented in table 1.

### Primary outcome measures

#### Interpretation bias (near transfer)

*Scrambled sentences test* (based on ref. 51): The scrambled sentences test involves reordering a list of words to form sentences. Participants use five of six presented words to form grammatically correct sentences, which can either be of negative or positive valence. For example, ‘looks the future bright very dismal’ may be unscrambled to form the sentence ‘the future looks very bright’ (positive) or ‘the future looks very dismal’ (negative). Participants are told to form the first sentence that comes to mind (rather than select a particular valence). In the present study, participants unscramble 20 sentences in 5 min, while holding in mind a string of six digits, as such a cognitive load depletes cognitive resources and is thus thought to present a truer reflection of participants' interpretative style.^51^ Half the sentences are related to worry themes (see themes above) and were generated by the authors, while half are related to depressive rumination and were selected from Wenzlaff and Bates^51^ and Wenzlaff and Bates.^52^ The number of negative sentences divided by the total number of grammatically correct sentences generated serves as an index of interpretation bias, with a higher index (scores range from 0 to 1) denoting a more negative interpretation bias. The test can be scored across all items or for worry and depressive rumination items separately. The scrambled sentences test is administered at the first and second study visit; thus, two separate lists of 20 items were created and the order is counterbalanced across participants.

*Recognition memory test* (based on ref. 16): The recognition memory test consists of two parts. In the first part, participants read 20 ambiguous scenarios, make a fragment completion judgement on the final word (see example below) and answer a comprehension question for each scenario. In the second part, participants are prompted with the title of each scenario and are presented with four statements for each scenario. Two statements relate to the resolution of the ambiguity in the scenario (targets), while the other two statements do not relate to the ambiguity (foils). In each pair of targets and foils, one statement is positive and one negative in valence. Participants rate how similar each presented statement is to the content of the original scenario, with greater similarity ratings for positive targets indicating a more positive interpretation of that scenario (and vice versa for negative targets). Foils are included to assess a general valence effect. The recognition test is relatively opaque in terms of its purpose and is not subject to demand or selection bias (see ref. 14 online supplementary materials A).

Of the 20 scenarios, half are related to worry (taken from refs. 16 and 46, with some slight wording changes) and half relate to depressive rumination (created by the authors). An example item developed for the experiment is shown below, followed by the corresponding target and foil statements (A–D).

## The day trip

Friends of yours have organised a day trip. You have been feeling quite low and wonder whether to join them. In the end, you decide to go along. Afterwards, you think back over the day and how going along made you (f e – l) [feel].Did you go on a day trip with your family? (Yes/No)
You felt better after going on the day trip (positive target)Going on the day trip made you feel worse (negative target)The car journey went very smoothly (positive foil)The car broke down on the way home (negative foil)Participants complete the recognition memory test at the beginning and end of the first study visit (before and after the first online session) and at the second study visit; hence, three separate lists of 20 items were generated and the order is counterbalanced across participants.

### 

#### Levels of worry and rumination (far transfer)

*Breathing focus task*: The breathing focus task measures the frequency of negative thought intrusions, which often initiate RNT. Based on the original breathing focus task/worry task,^17^
^18^
^53^ participants focus on their breathing for 5 min and indicate at randomly cued intervals whether they are indeed focusing on their breathing or are experiencing a thought intrusion. Participants categorise thought intrusions as negative or otherwise and provide brief summaries of content. Participants then engage in worry (GAD group) or rumination (MDD group) about a salient current worry/rumination topic for 5 min, followed by another 5 min breathing focus period, with sampling as before. After each breathing focus period, participants are reminded of their summaries of each thought intrusion in turn and are asked to provide further details on their thoughts as they originally occurred. These expanded descriptions are audio-recorded and will later be categorised as negative or otherwise by an assessor who is blind to diagnostic group, condition and breathing phase (preperiod vs postperiod of worry/rumination).

*Self-report questionnaires*: Trait worry levels will be assessed using the Penn State Worry Questionnaire (PSWQ^54^) which comprises 16 items (eg, ‘If I do not have enough time to do everything, I do not worry about it’) rated on a scale from 1 (*not at all typical of me*) to 5 (*very typical of me*) and summed (after reverse-scoring appropriate items) to produce an overall score, with higher scores denoting greater worry. Trait rumination will be measured using the Ruminative Response Scale (RRS^55^), which comprises 22 items relating to the frequency of ruminative thoughts (eg, ‘think about how you don't seem to feel anything anymore’) rated on a scale from 1 (*almost never*) to 4 (*almost always*) and summed, with higher scores denoting greater rumination. Participants will also complete a 15-item ‘RNT questionnaire’ (RNTQ) developed for the study that assesses key aspects of RNT and its consequences (eg, frequency of RNT; extent to which participants actively try not to engage in RNT; degree of difficulty controlling RNT; ability to concentrate; extent of catastrophising). Items will be completed in relation to the previous week.

### Secondary outcomes

#### Levels of anxiety and depression (far transfer)

Depressive symptoms will be assessed with PHQ-9^37^ and anxiety symptoms will be assessed using the GAD-7.^38^ These measures are widely used in research and clinical settings, allowing us to draw comparisons with experimental studies and clinical interventions.

#### Inhibition of distracting emotional information

*Classic Stroop and emotional Stroop tasks:* The classic Stroop task^56^ consists of presenting a list of colour words printed in different coloured ink with the instruction to read aloud the ink colour rather than the word itself. The first list (congruent) shows colour words printed in their congruent ink colour (eg, ‘blue’ written in blue ink); the second list (incongruent) features colour words printed in an incongruent ink colour (eg, ‘blue’ written in green ink) and participants must inhibit the meaning of the word to succeed in reading the ink colour. The ink colours and words used in the present study are ‘red’, ‘white’, ‘yellow’, ‘green’ and ‘blue’. Words are presented on a black background. The classic Stroop is followed by an emotional Stroop task, in which three lists, namely, anxiety-related (eg, nervous, criticised), depression-related (eg, tearful, despair) or neutral (eg, umbrella, writing) words are presented in varying ink colours. We drew on previous studies^57–60^ to construct the emotional Stroop; each word list comprised 15 words. Lists were matched for word length and frequency in the English language. Words were repeated five times and printed in five colours (same colours as for classic Stroop above); thus, each list comprised 75 words printed in a pseudorandom order in five vertical columns of 15 words each against a black background. The order of presentation for the different word lists is counterbalanced across participants and study visits. For classic and emotional Stroop tasks, participants read the ink colour out loud to the experimenter. The number of errors made and time latencies (seconds) are recorded for each list; time latencies constitute the outcome variable, and classic and emotional Stroop tasks are analysed separately.

### Additional measures relating to the experimental conditions

*Expectancy and acceptability ratings**:* Items to measure study expectancy and acceptability will be adapted from Williams, Blackwell, Holmes and Andrews.^39^ At the first study visit, participants will be asked, ‘At this point, how logical does the programme offered to you seem?’ and ‘How useful do you think this programme will be in reducing your depression/anxiety symptoms?’; at the second study visit, they will be asked, ‘After having completed the programme, how logical was the programme offered to you?’ and ‘How useful was this programme in reducing your depression/anxiety symptoms?’. Participants respond on a five-point scale from 0 (*not at all logical/useful*) to 4 (*very logical/useful*).

*Assimilation and imagination ratings*: Participants will complete nine items adapted from Standage, Harris and Fox^61^ and Holmes, Mathews, Dalgleish and Mackintosh^46^ to investigate the degree to which they assimilate the content of scenarios (‘While listening to the scenarios, how much did you think they were describing reactions that you could not imagine yourself having?’), are able to imagine themselves in the scenarios (‘While listening to the scenarios, to what extent could you see yourself in the scenarios, as though they were happening to you?’) and how vividly they were able to imagine the scenarios (‘How vividly did you imagine the situations that were described?’) on visual analogue scales (0–100).

*Ratings of worry, rumination, anxiety and depression during CBM-I/control sessions (manipulation checks)*: During each online session, participants will complete ratings of worry, rumination, anxiety and depression immediately after the worry/rumination induction/filler task, and at the end of the session. Single-item questions assessing current level of worry, rumination, anxiety and depression will be presented as visual analogue scales (0–100). Mean ratings will be compared across conditions to assess that the worry/rumination induction differs from the neutral task as intended.

### Procedure

Participants will be invited to take part in a research study into worry and rumination which includes two face-two-face study visits scheduled 3 weeks apart, nine homework sessions to be completed online between study visits and a follow-up questionnaire to be completed online 1 month after the second study visit (see figure 2 for participant flow through the components of the study). Prospective participants will be recruited from the community and from King's College London. They will complete an initial screening questionnaire online, including the PSWQ, RRS, PHQ-9 and GAD-7. If they meet inclusion criteria, the SCID will be completed by a trained researcher to confirm a diagnosis of GAD or depression. Once enrolled, participants will complete a presession questionnaire including standardised measures (PSWQ, RRS, PHQ-9, GAD-7, RNTQ) as well as demographic information online within 24 hours prior to the first study visit (experimental session). Should participants indicate risk to themselves (a score of >1 on PHQ-9 suicidal ideation item) on the preassessment questionnaire, this will trigger a risk assessment at the study visit.

**Figure 2 BMJOPEN2016013404F2:**

Participant flow chart with measurement points.

At the first study visit (experimental session), participants provide written informed consent and will be randomised by diagnostic group to one of the three conditions: (1) CBM_RNT, (2) CBM_STAND or (3) CONTROL (see the Experimental conditions section above for details). They will then complete the scrambled sentences test, classic and emotional Stroop task, recognition memory test and breathing focus task. Then, participants will be given the study rationale for the online homework sessions and will complete expectancy and acceptability ratings before completing the first online session on the study website. This is completed during the study visit to ensure participants understand the instructions for their condition and are able to complete the sessions correctly. Each session includes the RNT induction (CBM_RNT) or neutral task (CBM_STAND and CONTROL conditions), followed by 50 scenario audio clips (see above) with a short break after 25 scenarios. In addition, participants complete ratings of state levels of worry, rumination, anxiety and depression after the prescenario task (RNT or neutral task) and at the end of each session. Following the first online session, participants complete the recognition memory test again (different scenarios; see above) to assess change from pre to post first study visit. Finally, participants are presented with instructions for completing the nine online sessions over the course of the next 3 weeks, and the researcher will complete a diary card with each participant to help schedule the homework sessions.

Participants will complete three online sessions per week over the next 3 weeks, with some flexibility in terms of dates and times of day, and with the provisos that they complete no more than one homework session per day and complete the homework sessions within 1 month and the final session no later than the day before their second study visit. Researchers will monitor adherence to the homework sessions using the online platform. They will keep in touch with participants by using participants' preferred method of contact (email, phone, SMS) to facilitate engagement and trouble shoot issues with the online sessions, and will encourage participants to catch up missed sessions. Participants are required to complete a minimum of eight sessions (see also the Statistical methods section).

Up to 24 hours before returning for their second study visit, participants will again complete the presession questionnaire (PSWQ, RRS, PHQ-9, GAD-7, RNTQ), and additionally will complete a ‘negative events form’ in relation to the previous 3 weeks to assess incidence of mental health-related events (eg, deterioration in symptoms, suicidal intent, hospitalisation, etc). Any events reported will be addressed with the participant at the second study visit; events may also be captured during other points of the study and will be addressed with the participant when they are raised. If the event is related to an aspect of the study, an adverse events form will be generated, which will be reviewed by the Research Steering Committee. At the second study visit, participants will again provide written informed consent for this visit, will complete treatment expectancy and acceptability ratings, assimilation and imagination ratings (in reference to the past nine sessions), and will then complete the scrambled sentences test, classic and emotional Stroop task, recognition memory test and breathing focus task before being debriefed and partially paid for their participation to date. One month after their second study visit, participants will complete the follow-up questionnaire online, which is identical to the presession questionnaire for study visit 2, and receive the final payment for their participation. The experimenter will contact participants for further information should any negative events and/or mental health-related events be reported at follow-up. Participants will receive £130 for their participation in the study.

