### Monitoring adverse events

Adverse events (significant and prolonged increases in anxiety and/or depressive symptoms related to taking part in the study) will be recorded and reported to the Research Steering Committee at the end of the study. Serious adverse events (potentially life-threatening events, eg, suicide attempt, hospitalisation due to mental health, death, related to taking part in the study) will be reported immediately to the Chair and Deputy Chair of the Research Steering Committee. In addition, we will record other negative life events reported by participants.

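### Both scheduled harm enquiries depend on returning for visit 2, so participants who do not return have no planned harm or symptom measurement after baseline

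*Protocol article*

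**What the plan says.** All references are to the protocol article.

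- **First scheduled enquiry (Procedure).** "Up to 24 hours before returning for their second study visit, participants will again complete the presession questionnaire". The set includes the PHQ-9 and GAD-7. A negative events form is added at this point, "in relation to the previous 3 weeks to assess incidence of mental health-related events".
- **Second scheduled enquiry (Procedure).** "One month after their second study visit, participants will complete the follow-up questionnaire online". Its content is stated as "which is identical to the presession questionnaire for study visit 2".
- **Unscheduled capture (Procedure).** "events may also be captured during other points of the study and will be addressed with the participant when they are raised".
- **Contact between visits (Procedure).** "Researchers will monitor adherence to the homework sessions using the online platform". Researchers also keep in touch by email, phone or SMS, with the stated aim "to facilitate engagement and trouble shoot issues with the online sessions, and will encourage participants to catch up missed sessions".
- **Session ratings (Additional measures relating to the experimental conditions).** Anxiety and depression are rated on 0–100 scales twice in each online session, as manipulation checks.
- **Definition (Monitoring adverse events).** An adverse event is "significant and prolonged increases in anxiety and/or depressive symptoms" related to taking part. The section sets out recording and reporting. It gives no schedule of enquiry and no rule for people who do not return.

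**The concern.** The plan's own definition of an adverse event needs symptom measurement after baseline, and over long enough to show that an increase lasted. The instruments that could show this are given only at two points, and both are reached by way of visit 2. Someone who worsens and therefore does not come back is the person this schedule cannot see.

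The sample makes this matter. Participants have diagnosed GAD or a current major depressive episode. Under Participants and recruitment, PHQ-9 totals up to 23 and a score of 1 on the suicidal ideation item remain eligible. Nine of the ten sessions are done at home. One arm begins every session with five minutes of induced negative thinking. It is plausible, though the documents do not show it, that worsening would contribute to not returning.

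This is separate from the completers-only rule under Statistical methods. That rule is justified by the mechanistic aim and governs the analyses. It gives no reason to stop asking about harm.

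**Working it through.** **Step 1: which routes reach a participant who does not return for visit 2?**

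| Route | Section | Reaches a non-returner? |
|---|---|---|
| Questionnaire and negative events form | Procedure | No; timed by the return visit |
| Online follow-up | Procedure | No; dated from visit 2 |
| Capture at other points | Procedure | Possibly; unscheduled |
| Contact between visits | Procedure | Possibly; the stated purpose is engagement and technical help |
| Session ratings | Additional measures | Only up to the last session done, so they cannot show a lasting increase afterwards |
| Adverse event rules | Monitoring adverse events | Only once an event is known |

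No route gives a scheduled harm enquiry, or a post-baseline PHQ-9 or GAD-7, to someone who does not return.

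**Step 2: how much could be missed?** The article states no figure to reproduce. It says drop-out will be summarised but gives no expected rate, and it gives no event rate. What follows is an illustration under assumptions.

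Let d be the proportion not returning, p the event rate in returners, and R the event rate in non-returners divided by that in returners. The share of events falling outside scheduled enquiry is

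d·R·p / [d·R·p + (1 − d)·p] = d·R / [d·R + (1 − d)].

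The rate p cancels, so only d and R need to be assumed.

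| d | Non-returners of 120 | R = 1 | R = 2 | R = 4 |
|---|---|---|---|---|
| 10% | 12 | 0.10/1.00 = 10% | 0.20/1.10 = 18% | 0.40/1.30 = 31% |
| 15% | 18 | 0.15/1.00 = 15% | 0.30/1.15 = 26% | 0.60/1.45 = 41% |
| 20% | 24 | 0.20/1.00 = 20% | 0.40/1.20 = 33% | 0.80/1.60 = 50% |

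The 120 is the abstract's 60 plus 60; the shares do not depend on it. In counts, if p is assumed to be 5%, the 10% row gives 0.6 of 6.0 events missed at R = 1 (12 × 0.05 against 108 × 0.05 = 5.4 in returners), 1.2 of 6.6 at R = 2 and 2.4 of 7.8 at R = 4. These shares are upper limits on what is lost, because unscheduled capture may recover some events.

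**Step 3: does this distort a comparison between arms?** If the missed share is the same in every arm, all counts shrink by the same factor and their ratio is unchanged. An excess in CBM_RNT would be understated in relative terms only if the missed share were larger there, that is, if worsening-related non-return were more common in that arm. The documents give nothing by arm on drop-out or worsening.

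**The case against.** The strongest reply is that this is a condensed article describing the ordinary participant's path. It does not say that the online form is withheld from someone who misses visit 2, and a full protocol may provide for contact at withdrawal. Researchers also watch adherence and chase missed sessions, so a person who goes quiet would be noticed and could report a problem. Serious events related to the study are reported at once when known.

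Part of this stands. The point must be put as what the article schedules, and it would be wrong to say that non-returners are never asked or are abandoned. But the article does more than stay silent: it describes harm collection and fixes its timing by the return visit. Followed as written, that timing leaves a gap, and no later analysis document can recover data that were not collected. Contact for engagement may bring an event to light, but it is not a harm enquiry.

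Three stronger readings are tempting and are not supported:

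- **That everyone who stops training goes unasked.** Both enquiries hang on attending visit 2, not on completing sessions. Statistical methods treats eight or more sessions and timely return as separate conditions, and nothing bars a person with fewer sessions from visit 2. Someone who stops the homework but attends gets both enquiries.
- **That a planned safety comparison is biased towards no difference.** No between-arm safety comparison is stated, and the direction of any bias depends on the condition in Step 3.
- **That a third to a half of events are lost.** That range needs the assumed fourfold rate in non-returners.

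**Conclusion.** The concern holds for participants who do not return for visit 2. As described, they have no scheduled harm enquiry and no planned PHQ-9 or GAD-7 after baseline, so adverse events as the plan defines them may be under-counted.

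The size is unknown. At 10% to 20% non-return, the share outside scheduled enquiry is 10–20% with equal event rates, 18–33% with twice the rate in non-returners and 31–50% with four times the rate. Both the non-return proportion and the rate ratio are assumptions. Some loss occurs in every case where non-returners have events. Nothing firmer can be said about differences between arms.

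This should be changed: the gap lies in the data collected from a vulnerable sample, and the remedy uses forms that already exist.

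**What to change.** - Send the existing online questionnaire and negative events form to every randomised participant at the planned visit-2 date (three weeks after visit 1), whether or not they attend and however many sessions they have done.
- Keep the follow-up at one month after visit 2 for those who attend. For non-returners only, send it one month after the planned visit-2 date. Re-dating it for everyone would shift an efficacy time point partway through the trial.
- Ask the reason when someone stops.
- Report events by condition for all randomised participants, with the number who answered each enquiry.

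The cost is an automatic link to forms already online, one added question, and staff time to read the replies. No new visit is needed. Response among non-returners will be incomplete, so the gap narrows but does not close. The change can reach only participants who have not yet finished: Protocol version and status reports that recruitment was continuing and that 59 had completed when the article was submitted. Earlier non-returners will mostly lack these data, and the report should say so.
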